### **5.3 Serious Adverse Events**

Serious adverse events will be defined as hospitalization or mortality. In the ADRD-MCC population we anticipate a baseline hospitalization rate of up to 30% due to morbidity burden.

### **5.4 Reporting procedures**

#### **Follow-up for Adverse Events Reported by Clinic Staff**

For any reports from clinic staff of PCPs, the KPCO PI will contact the PCP to review the potential concern and will refer the participant's record for chart abstraction as described above. All potential concerns will be noted and discussed with the DSMB at regular meetings (or immediately for any serious adverse event potentially due to the intervention) and will be reported to the KPCO IRB. Any serious adverse events likely to have resulted from the intervention will be reported to the KPCO IRB, the DSMB and NIA within 5 calendar days. Concerns unlikely to have resulted from the intervention will be summarized for routine DSMB reporting in a separate table prepared by the study biostatistician. Any Serious Adverse Event affecting immediate patient safety will be reported to the KPCO IRB, DSMB, and NIA within 24 hours by

one of the study PIs. Follow-up will extend until discharge from the hospital for hospitalizations or completion of any acute care services associated with an adverse event.

## **5.5 Safety Monitoring**

The Chair of the DSMB will serve as the Safety Officer. DSMB members will not be blinded to intervention groups. DSMB meetings to review safety data will be held at least twice yearly with additional meetings at the discretion of the DSMB chair.

## **6 INTERVENTION DISCONTINUATION**

For this pragmatic intervention, there are no specific intervention discontinuation criteria. The chair of the DSMB will serve as data safety monitor. All clinicians will be able to directly report any safety concerns as described above. Although individual patients/ care partners and clinicians will receive intervention materials, none are required to act on the materials or to participate in deprescribing discussions at any point. This is made explicit in the introductory letter to patients that accompanies intervention materials. Outcomes data will be collected regardless of whether patients / care partners and PCPs in intervention and control clinics choose to discuss medication management or deprescribing. The KPCO IRB may request study cessation.

## **7 STATISTICAL CONSIDERATIONS**

### **7.1 General Design Issues**

The study design is a pragmatic, primary care-based trial of deprescribing education for patients/ care partners and clinicians which will be randomized at the level of the clinic. The primary hypothesis is that this patient-centered intervention will reduce number of chronic medications and percent of individuals taking one or more PIMs among seniors with ADRD-MCC.

### **7.2 Sample Size and Randomization**

#### **Sample Size and Randomization**

There will be 9 intervention clinics and 9 control (delayed intervention clinics). We estimated power using members who would be eligible for the intervention in November 2018. Feasibility data for that cohort showed a median of 5 visits in the prior year with 99% having at least one visit and 80% scheduling a visit at least 7 days in advance. Patient materials are sent in advance of visits only for appointments made at

least 7 days before a visit, therefore, we anticipate approximately 80% of the eligible intervention population will receive mailings during the study period.

We identified 3,671 eligible members with numbers per clinic ranging from 60 to 350. For analyses of counts of medications, we will have > 80% power to detect a decrease of -0.70 (i.e. < 1 medication; power from difference in two Poisson rates in cluster-randomized trial given event rate of 6.8 and intraclass correlation coefficient (ICC)=0.01). We will be examining selected subgroups of interest, for example cohort members receiving a higher dose of the intervention or a restricted cohort with more severe dementia. Both of these comparisons could reasonably retain ~70% of the intervention cohort to contrast to the control cohort and we would be able to detect a decrease of 1.4 medications even if ICC was doubled (i.e. 0.02). Comparisons of proportions of members on a PIM will be able to detect a decrease to 29.0% or less for the intervention clinics compared to the expected rate of 35.8% for the control clinics.

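### The detectable fall in PIM use (35.8% to 29.0%) has about 72% power, not 80%, if the paragraph's own ICC of 0.01 is combined with a two-sided 5% test

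*Protocol*

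**What the plan says.** Everything relevant to power is in Protocol section 7.2, Sample Size and Randomization.

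- Design: "There will be 9 intervention clinics and 9 control (delayed intervention clinics".
- Size: "We identified 3,671 eligible members with numbers per clinic ranging from 60 to 350".
- Medication counts: "we will have > 80% power to detect a decrease of -0.70", with the basis given as "power from difference in two Poisson rates in cluster-randomized trial given event rate of 6.8 and intraclass correlation coefficient (ICC)=0.01".
- PIM use: "Comparisons of proportions of members on a PIM will be able to detect a decrease to 29.0% or less for the intervention clinics". The control figure set against this is 35.8%.
- Exposure: "we anticipate approximately 80% of the eligible intervention population will receive mailings during the study period".

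The power level and the base-case ICC are written in the sentence on counts. The only other ICC in the section is 0.02, used for a subgroup comparison of counts. The PIM sentence has neither a power level nor an ICC, and the protocol states no alpha or sidedness. Sections 7.1 and 7.4 make PIM use one of the two primary outcomes. Section 7.5 plans multilevel models with adjustment for baseline medication use, but section 7.2 does not say that the PIM figure takes credit for it.

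**The concern.** A statement that a trial can detect a given difference has meaning only at a given power, error rate and ICC. A reader of section 7.2 will take the PIM sentence on the terms just given for counts, and will assume a conventional two-sided 5% test. On those terms the figure falls short.

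The consequence is for interpretation. If the PIM comparison is null, the stated 29.0% invites the conclusion that a fall of 6.8 percentage points was reliably ruled out. At about 72% power, a true fall of that size would be missed in roughly 28% of such trials, not 20%.

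**Working it through.** **Inputs from section 7.2.** 9 clinics per arm; 3,671 members, so 1,835.5 per arm and 3,671/18 = 203.9 per clinic; proportions 0.358 and 0.290; ICC 0.01, carried over from the count sentence.

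**Assumed, because the protocol is silent.** Alpha 5%, tried two-sided and one-sided; equal clinics and a normal reference in the base case.

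**Design effect and effective size**
- DE = 1 + (203.9 − 1) × 0.01 = 3.03
- Effective n per arm = 1,835.5 / 3.03 ≈ 606

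**Standard error and signal**
- SE = √[(0.358 × 0.642 + 0.290 × 0.710) / 606] = √(0.4357 / 606) = 0.0268
- 0.068 / 0.0268 = 2.54

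**Reproducing the stated figure**
- One-sided 5%: Φ(2.54 − 1.645) ≈ 0.81. The detectable proportion at 80% power is 29.1%, which matches the stated 29.0%.
- Two-sided 5%: Φ(2.54 − 1.96) ≈ 0.72. The detectable proportion at 80% power is 28.3%, which does not match.

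Pooled-variance and arcsine versions of the two-sided calculation both give 71.6%.

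**What would give 80% power two-sided**
- Required effective n per arm = (1.960 + 0.842)² × 0.4357 / 0.068² ≈ 740
- By ICC: (1,835.5/740 − 1) / 202.9 ≈ 0.0073
- By baseline adjustment, taking the variance reduction as 1 − r²: r = √(1 − 606/740) ≈ 0.43

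**Sensitivity at ICC 0.01.** The size CV of 0.36 is an assumption: a quarter of the stated range over the mean, (290/4)/203.9. Unequal clinics enter as DE = 1 + [(1 + CV²)m − 1] × ICC. The 80% rows put 0.8 × 3,671 ≈ 2,937 members in the analysis, 163.2 per clinic.

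| Case | Two-sided 5% | One-sided 5% |
|---|---|---|
| All 3,671, equal clinics, normal | 72% | 81% |
| All 3,671, CV 0.36, normal | 68% | 78% |
| All 3,671, equal clinics, t on 16 df | 66% | 78% |
| 80% of members, equal clinics, normal | 68% | 79% |
| 80% of members, CV 0.36, t on 16 df | 60% | 73% |

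In the last row the two-sided detectable proportion at 80% power is about 27.2%.

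**Sensitivity to the ICC** (all members, equal clinics, normal, two-sided): 0.005 gives 87%; 0.02 gives 50%.

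**Count outcome as a cross-check.** SE = √[(6.8 + 6.1) × 3.03 / 1,835.5] = 0.146, and 0.70/0.146 = 4.8, so two-sided power is above 99%. The count statement is true and does not help to settle which test was intended for PIM use.

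**The case against.** The strongest reply is that the figure is under-specified rather than wrong. The hypothesis is directional, no sidedness is stated, and a one-sided 5% test with equal clinics reproduces 29.0% almost exactly. ICC 0.01 is written for counts, and a binary outcome may have a different ICC; at about 0.007 the figure holds two-sided. Section 7.5 plans baseline adjustment, and at an assumed correlation of 0.5 two-sided power would be about 83% (78% with t on 16 df). Test details may also be fixed in an analysis plan that is not shown.

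Most of this stands. It means that 72% cannot be called a ceiling, although a reader might infer that. It does not rescue the sentence as written. A directional hypothesis is not a one-sided test, and section 7.2 claims neither a lower ICC nor credit for baseline adjustment. The one-sided reading is also fragile: unequal clinics, a t reference or a cohort cut to 80% each take it just below 80%. Leaving details to an analysis plan does not excuse a figure in the protocol that its own paragraph does not support on the usual reading.

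Three stronger readings are tempting and are not supported:

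- **That power is about 60% on the protocol's own facts.** That figure needs an assumed CV, a t reference and restriction of both arms to 80%. Section 7.2 applies the 80% to mailings in the intervention population, while section 7.5 bases the primary analyses on all eligible members. The baseline definition in section 4.2, tied to mailing or to a first appointment, points the other way. The analysed number is therefore unclear, not established as the smaller one.
- **That power should be cut further for unmailed patients or for two primary outcomes.** The clinician component can reach unmailed patients, and the protocol states no split of alpha.
- **That the count figures are also wrong.** Power above 80% for a fall of 0.70 is conservative, but true.

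**Conclusion.** The point holds in a limited form. Using the clinic and member numbers in section 7.2 and its base-case ICC of 0.01, power to detect 35.8% versus 29.0% at two-sided 5% is about 72%, and the detectable value at 80% power is about 28.3%. This rests on three readings: that the power level and ICC of the count sentence apply to PIM use, that the test is two-sided at 5%, and that no credit is taken for baseline adjustment. The stated figure is recoverable only through a one-sided test with equal clinics, a smaller ICC or a baseline correlation of about 0.43 or more, and none of these is stated. The 60% and 27.2% are a sensitivity case under added assumptions, not the finding.

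**What to change.** In section 7.2, replace the PIM sentence with one of two statements, both at two-sided 5%, ICC 0.01 and all 3,671 members:

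- 80% power for a fall from 35.8% to about 28.3%; or
- about 72% power for a fall to 29.0%.

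Give the alpha, sidedness, ICC, analysed number and any assumed baseline correlation for this outcome. If unequal clinic sizes or the mailed cohort are the intended basis, quote the correspondingly lower detectable value and the size CV used. If a one-sided test, a different ICC or credit for baseline adjustment was intended, say so and justify it. The 29.0% can then stay, provided that it reproduces from the stated inputs.

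The cost is a less favourable figure or a fuller justification. No clinics, patients or analyses change.

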#### 7.2.1 Treatment assignment procedures

The intervention will be a cluster randomized trial delivered at the clinic level with a delayed control design so that all potentially eligible KPCO members will have the opportunity to receive enhanced medication management. Outcomes will be measured at the level of the individual. Clinics will be randomized in blocks of two based on the number of eligible patents. In past experience this has balanced patient characteristics, but we will confirm comparability of the key variables for this study between the intervention and delayed control clinics and consider different blocking schemes if appropriate. Limited remaining differences will be described and adjusted for in statistical analyses.

### 7.3 Interim analyses and Stopping Rules

Please see discussion of adverse events above. There are currently no statistical criteria that would suspend the intervention.

Every 3 months we will compare rates of hospitalizations and mortality between groups who have received the intervention (have been sent a mailing) from intervention clinics, and those who would have been eligible to receive the initial mailing from control clinics. These rates will be reported to the DSMB.

There will be ongoing safety monitoring using chart abstraction as described above. Any serious adverse events potentially due to the intervention will be reviewed with the KPCO IRB and with the DSMB Chair who will serve as the Safety Officer.

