## **5.2 Methods and Timing for Assessing, Recording, and Analyzing Safety Parameters**

There are two primary elements to the safety monitoring plan: comparing rates of potential serious adverse events between intervention and control clinics; and chart abstractions of a sample of patients who experience a potential serious adverse event in each group.

Comparing rates of potential serious adverse events: Every 3 months rates of hospitalizations, and mortality will be compared between groups who have received the intervention (have been sent a mailing) from intervention clinics, and those who would have been eligible to receive the initial mailing from control clinics. These rates will be reported to the DSMB at usual meetings. Chart Abstractions: These will be conducted on all deaths and a sample of every third hospitalization to determine if the potential serious adverse event occurred within 4 months of a medication adjustment by the patient’s primary care physician. Causality related to the medication adjustment will be reviewed in a blinded fashion by steering committee investigators ([name], [name], [name]). Findings will be reported to the DSMB at usual meetings. Study PIs ([name], [name]) are blinded to the safety monitoring process which is led by the study biostatistician.

All deaths among individuals who have received the intervention from intervention clinics, and those who would have been eligible to receive the initial mailing from control clinics will be reviewed by a trained Pharm D chart abstractor to determine whether the death occurred within 4 months of a medication

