adjustment by the patient's primary care physician. Similarly, every third hospitalization for these two groups will be reviewed to determine the primary diagnosis for that hospitalization and whether the potential serious adverse event occurred within 4 months of a medication adjustment by the patient's primary care physician. (The abstraction sample will be generated weekly.) The PharmD medical record abstractor, a member of the KPCO pharmacy department, will access the tracking database and will review each record using a chart abstraction tool. Records provided to the PharmD will not indicate intervention versus delayed control status but the PharmD cannot be fully blinded due to potential evidence in staff messages related to the study in some charts. In addition to avoiding study status identification on records sent to the PharmD, potential bias will be minimized by detailed chart data extraction steps to be consistently followed.

Throughout the study period any physician, pharmacist or health care staff member will be able to report concerns about a safety issue that arises via an email or phone call to the KPCO Project Manager or the KPCO PI. All clinician Tip Sheets will include contact information for the KPCO PI.

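### About 20% of eligible intervention-clinic patients fall outside the quarterly safety comparison and routine chart review, although the clinician education can reach them

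*Protocol*

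**What the plan says.** Protocol section 7.3 defines the intervention side of the three-monthly comparison of hospitalization and mortality as "groups who have received the intervention (have been sent a mailing) from intervention clinics". Section 5.2 repeats this and sets against it "those who would have been eligible to receive the initial mailing from control clinics".

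The systematic chart review in section 5.2 covers the same people. For deaths the set is "All deaths among individuals who have received the intervention from intervention clinics, and those who would have been eligible to receive the initial mailing" at control clinics; for admissions, "every third hospitalization for these two groups will be reviewed".

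Section 7.2 gives the expected reach of the mailing: "we anticipate approximately 80% of the eligible intervention population will receive mailings during the study period". A patient is mailed only if a primary care visit is booked at least 7 days ahead.

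The clinician component in section 3.1 has no such condition. The opening presentation and the Tip Sheets are meant for all internal and family medicine primary care physicians at the intervention clinics. Only the appointment note in the record depends on a mailing having gone out.

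**The concern.** Randomization is by clinic, and one of the two intervention components acts on the clinician. A physician who has attended the presentation and received Tip Sheets may stop a medication in any eligible patient, mailed or not. Section 5.1 names the harms that could follow such a decision, such as recurrent symptoms and withdrawal events. The chart review asks whether an event came within 4 months of a medication change by the primary care physician. An unmailed patient of an educated physician can meet that description and still be in neither the rates nor the review.

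The DSMB tables carry much of the weight: section 7.3 has no statistical criterion for suspending the intervention, and section 6 has no specific discontinuation criteria. The safety set also looks narrower than the efficacy set, because section 7.5 plans the primary analyses on all members who meet eligibility. A drug stopped in an unmailed patient could count toward benefit, while a later admission or death would not enter the safety comparison.

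**Working it through.** **Step 1: reproduce the 80%.** Section 7.2 reports feasibility data of "99% having at least one visit and 80% scheduling a visit at least 7 days in advance".
- If the 80% refers to all eligible members, the mailed share is 0.80.
- If it refers only to those with a visit, the mailed share is 0.99 × 0.80 = 0.792.

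Both agree with the stated projection.

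**Step 2: share outside the safety set.**
- All unmailed: 1 − 0.80 = 0.20, or 1 − 0.792 = 0.208.
- Unmailed but with at least one visit: 0.99 − 0.80 = 0.19, or 0.99 × 0.20 = 0.198. The other 1% had no visit in the feasibility year.

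**Step 3: number of patients.** Section 7.2 states: "We identified 3,671 eligible members with numbers per clinic ranging from 60 to 350". The split by arm is not given. Assuming equal arms, 3,671 / 2 = 1,835.5 per arm.

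| Group | Share | Intervention-arm patients |
|---|---|---|
| Seen, unmailed | 0.19 | 349 |
| Seen, unmailed (second reading) | 0.198 | 363 |
| All unmailed | 0.20 | 367 |
| All unmailed (second reading) | 0.208 | 382 |

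The control set is restricted in the same way, so about 0.20 × 3,671 = 734 patients over both arms are left out.

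**Step 4: earlier reviews.** The 20% is the position at the end of 12 months. Clinicians are educated at the start, but a patient enters the safety set only when mailed. The protocol gives no accrual curve, so two patterns are assumed, both reaching 80% at month 12:
- steady numbers: share outside = 1 − 0.80 × t/12
- constant rate among those not yet mailed: share outside = 0.20^(t/12)

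| Month | Steady numbers | Constant rate |
|---|---|---|
| 3 | 80% | 67% |
| 6 | 60% | 45% |
| 9 | 40% | 30% |
| 12 | 20% | 20% |

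Some of those outside the set early on will not yet have seen their physician, so these figures bound exposure and do not measure it.

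**Step 5: the populations side by side.**

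| Purpose | Population | Section |
|---|---|---|
| Clinician component | all internal and family medicine physicians at intervention clinics | 3.1 |
| Primary efficacy analysis | all members meeting eligibility | 7.5 |
| DSMB remit | all study participants | 9.1 |
| Quarterly rates | mailed patients and control equivalents | 5.2, 7.3 |
| Routine chart review | the same two groups | 5.2 |

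The last two rows are narrower than the rest.

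**The case against.** **The restriction can be defended as deliberate and fair.** Section 4.2 ties baseline to the identified appointment and the mailing, and says control patients are screened by the same methods. The safety set follows that definition, so it compares like with like. It looks where both components act and where an effect is most likely. Section 5 says the monitoring was developed with the NIA and the DSMB. This stands, and it is why the existing comparison should be kept.

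**Unmailed patients are less exposed.** They get no brochure or questionnaire, and their physician gets no appointment note. Section 5.1 adds that the intervention does not itself stop any medication. This also stands. Their exposure is partial and comes only through the clinician, but it is not zero.

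**Four stronger readings are tempting, and the protocol does not support them.**
- *These patients are never monitored.* Any staff member may report a concern, and a report leads to chart abstraction and DSMB discussion (sections 5.2 and 5.4). The DSMB may also ask for further information (section 9.1). Section 7.4 lists hospital admissions as a secondary outcome, and mortality is in the 12-month schedule. However, staff reports are voluntary and give no rate by arm. Secondary outcomes come after the primary analyses. The schedule is dated from the mailing, so how unmailed patients would be captured there is unclear.
- *About 110 hospitalized patients a year are missed.* The product 367 × 0.30 = 110 uses the rate in section 5.3, which is an upper bound with no stated period. It also assumes equal arms. These would be mostly background admissions, not harms of the trial.
- *Unmailed patients are sicker.* Nothing in the protocol says so.
- *The comparison is biased.* The same rule applies to both arms, so no bias is evident.

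**Conclusion.** The point holds as one of coverage. By the protocol's own projection, about 20% of eligible intervention-clinic patients fall outside both the quarterly rates and the systematic chart review. That is roughly 349 (seen but unmailed) to 367 (all unmailed), and up to 382 on the second reading of the 80%. For them, voluntary staff reporting is the only defined safety route during the trial. More are outside at early reviews: 67% to 80% at month 3 under the assumed accrual patterns.

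The result rests on an equal split of the 3,671 members, on a planning projection of 80%, and on clinician education being able to change prescribing for unmailed patients. That the safety set is narrower than the efficacy set rests on the wording of section 7.5; because baseline is tied to the mailing, the place of unmailed patients in the efficacy analysis also needs to be made explicit. No excess risk has been shown or estimated. This is a cheap improvement, not a defect that invalidates the monitoring.

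**What to change.** Keep the mailed-versus-equivalent comparison in sections 5.2 and 7.3. Add to each DSMB report a table of hospitalization and mortality rates, with person-time, for all eligible patients by randomized arm.

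State one index date that is common to both arms and does not depend on the mailing, for example the start of the initial intervention period or the date of eligibility if later. Without it, unmailed patients have no start for person-time, because section 4.2 anchors baseline to the mailing.

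Sections 4.2 and 8.2 say that the Virtual Data Warehouse already holds enrollment, utilization and mortality data, so no new data collection is needed. The cost is defining the index date and producing one more table per report. The all-eligible contrast will be somewhat diluted by less exposed patients, so it should sit beside the present comparison and not replace it. Routine chart review can stay as it is. Deaths in unmailed patients would then appear in the rates without routine abstraction, and the DSMB could request abstraction if the rates diverge.
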